# Transcranial direct current stimulation in management of pain, mood, functionality, and quality of life in patients undergoing hemodialysis: a study protocol for a double-blind controlled randomized trial

**DOI:** 10.1186/s13063-019-3769-6

**Published:** 2019-12-30

**Keywords:** Brain stimulation, Kidney diseases, Pain, Depression, Quality of life

## Abstract

**Background:**

Persistent pain can lead to incapacitation requiring long-term pharmacological treatment. Up to 82% of chronic kidney disease (CKD) patients undergoing hemodialysis (HD) have chronic pain and most do not respond to usual medication. Advances in non-pharmacological treatments are necessary to promote pain relief without side effects and to restore functionality. Transcranial direct current stimulation (tDCS) promises to be a novel, cost-efficient, non-pharmacological treatment for CKD patients with chronic pain. In this study, we hypothesize that tDCS could improve pain, depression, functionality, and quality of life in patients with CKD undergoing HD.

**Methods/design:**

We describe a single-center, parallel-design, double blind randomized, sham-controlled trial. Forty-five subjects with CKD undergoing HD will be randomized to a motor cortex (M1), a dorso lateral prefrontal cortex (DLPFC), or a sham group. A total of ten sessions will be administered to participants over 4 weeks using a monophasic continuous current with an intensity of 2 mA for 20 min. Participants will be evaluated at baseline, immediately after the tenth session, and at 1 week and 4 weeks of follow-up after the intervention. Pain, depression, functionality, and quality of life will be evaluated.

**Discussion:**

The results from this study will provide initial clinical evidence on the efficacy and safety of tDCS in patients with CKD undergoing HD.

**Trial registration:**

Brazilian Clinical Trials Registry/Registro Brasileiro de Ensaios Clínicos (ensaiosclinicos.gov.br), 1111–1216-0137. Registered on 20 June 2018.

## Background

A complete physical and mood assessment is critical to provide an appropriate treatment plan for chronic kidney disease (CKD) [1]. Management of persistent pain in this population requires an adequate understanding of the pathogenesis and clinical conditions with the aim of improving life span and quality of life (QoL) [2]. Up to 82% of CKD patients undergoing hemodialysis (HD) experience chronic pain, and 35–70% of patients describe the pain as moderate to severe [1–3]. Chronic pain in CKD patients undergoing HD may be caused by various factors, including musculoskeletal, ischemic, abdominal, chest, and neuropathic pain [2, 3].

Chronic pain in CKD patients has been considered a genuine neurologic disturbance, and it co-occurs generally with many pain syndromes in the context of suffering throughout the lifetime [4, 5]. Studies suggest that long-term chronic pain may result in the development of adaptive neuroplasticity and functional reorganization, with a network shift from affective processing of salience to cognitive modulation of pain [6]. Pain-related regions are parts of the pain neuromatrix (medial prefrontal cortex, posterior cingulate cortex, and insula) and exhibit abnormal functional and structural changes in chronic pain when compared with those in healthy people [6]. These modulatory system regions are associated with chronic pain, cognitive control of emotion, and self-referential processing [6].

Pain is a major cause of depression, disturbed sleep patterns, impaired dialysis adequacy (if unable to endure full sessions), and likeliness of withdrawal from dialysis [3]. Several researchers have also shown that pain negatively impacts many aspects of QoL, including physical function, social function, daily activities, energy, fatigue, and emotional function [7]. Markers of both muscle mass and strength are important predictors of outcomes in this patient population and a decrease in these markers can contribute to risk of physical disability and cognitive decline [8].

In addition to medical therapies, adjunctive non-pharmacologic interventions must be considered whenever applicable for pain in CKD patients undergoing dialysis. Suboptimal pain control is associated with poor QoL, depression, and possibly long-term survival. Nonetheless, adequate medical pain control remains a challenge due to the potential for drug-induced complications and abuse and dependence. Clinicians and the research community should promote pain management in CKD patients undergoing dialysis as a clinical and research priority to improve their QoL and pain-related disability.

Recent studies have shown that novel neuromodulating techniques can have pain-relieving effects in the treatment of chronic pain [9–11]. Studies using anodal transcranial direct current stimulation (tDCS) of motor cortex (M1) or dorsolateral prefrontal cortex (DLPFC) have shown an improvement in pain and depression in several chronic pain syndromes [9]. Anodal tDCS has been shown to increase cortical excitability, promoting pain relief through indirect effects on pain-processing regions in the brain [12]. Promising results have been reported for pain in several diseases such as fibromyalgia, neuropathic pain, chronic post-stroke pain, low back pain, and pelvic pain [9].

tDCS emerges as a simple potential tool to improve QoL and functionality and shed light on the role of brain reorganization in pain function. For CKD patients with chronic pain, tDCS may represent an important cost-efficient, non-pharmacological treatment for a large number of patients with permanent chronic pain, depression, and disability. We currently have no evidence from randomized controlled clinical trials on the use of tDCS to treat pain and depression in CKD patients undergoing HD.

The primary objective of the current study is to evaluate the effects of anodal tDCS over M1 and DLPFC on pain in CKD patients undergoing HD. The secondary outcomes are to assess its impact on depression, anxiety, physical performance, and QoL.

## Methods

### Study design and recruitment

This protocol is presented in accordance with the SPIRIT Initiative 2013 (Additional file 1), an evidence-based guide for the content of trial protocols. This study is a single-center, parallel, randomized, sham-controlled trial in which patients and assessors will be blinded. Patients with CKD undergoing HD will be recruited at Instituto do Rim by invitation after the benefits of tDCS for chronic pain syndromes is explained to them. To help achieve adequate participant enrolment, flyers will be placed at the recruitment site and physicians will be informed of the study to assist with identifying potentially eligible participants.

This study will be conducted at the Federal University of Rio Grande do Norte, Natal, Brazil and registered with the Brazilian Clinical Trials Registry ReBec (www.ensaiosclinicos.gov.br/rg/RBR-7qk2cs/), registration number U1111–1216-0137; June 20, 2018. Data will be stored at Motricity Lab—Federal University of Rio Grande do Norte and will be archived with the principal investigator for 5 years and then destroyed. Possible changes to the protocol will be communicated to the local Ethics Committee, ReBec, and participants. Documents will not be made public without the permission of the participants and resulting publications will not identify the subjects.

All participants will be informed about the trial’s objectives and procedures and that participation is voluntary, as determined by resolution No. 466/12 of the National Health Council. Potentially eligible patients with CKD undergoing HD who are willing to know more about the study will receive a detailed study explanation from the study research coordinator, including objectives, procedures, risks, and benefits of the study and all questions will be answered. Interested patients will be asked to sign an informed consent form (Additional file 2) before entry into the study. Informed consent will be obtained by the research team before study assessments and study procedures are performed and before any private information is recorded. After agreeing to participate in the trial, all participants will sign the informed consent form, which was submitted and approved by the ethics committee of the Faculty of Health Sciences of Trairí—Federal University of Rio Grande do Norte (number 2.678.737). Adult patients assisted in the dialysis center will be recruited.

After the end of the study all patients who received the sham tDCS will be invited to do the active tDCS. Investigators will record the data collected and confidentiality will be guaranteed. Several post-recruitment retention strategies will be used to retain participants in this study and optimize follow-up data collection rates. All participants will be contacted by telephone and email to remind them of their follow-up assessments. Also, participants will receive email or mobile messages informing them about the contribution they are making by remaining in the study.

### Inclusion criteria

Patients will be included if they fulfill the following inclusion criteria: (1) male or female aged 18 to 75 years; (2) undergoing HD with ESRD (CKD 5D^2^) for > 3 months, (4-h session); (3) pain related with a score of more than 4 (range of scores from 1 to 10) in a visual analog scale (VAS) for > 3 months; (4) have physical capacity to do physical evaluation and be capable of consenting to treatment and understanding study explanations and questionnaires; and (5) provide informed consent.

### Exclusion criteria

Patients with any of the following criteria will be excluded from the study: (1) electrical implants in the body; (2) a history of epilepsy or convulsion; (3) clinically contraindicated to receive tDCS, such as having metal embedded in their scalp or brain; (4) psychiatric illness; (5) pregnant women; and (6) signs of severe disease and/or indication of hospitalization, including hemodynamic instability, infection, acute myocardial infarction, and stroke.

### Chronic kidney disease

According to Brkovic et al. [3], end stage renal disease (ESRD) is defined as loss of renal function requiring renal replacement therapy (RRT) with any form of chronic dialysis or renal transplantation, or occasionally conservative management in the elderly or those with significant comorbidities. Acute kidney injury requiring dialysis is not considered ESRD unless renal function fails to recover [3]. In addition, conservative management should be an option in people with ESRD and this should be supported by a comprehensive management program that includes protocols for symptom and pain management, psychological care, spiritual care, and culturally sensitive care for the dying patient and their family [13].

Dialysis patients report significantly more bodily pain, lower vitality, poorer general health, physical, mental, and social dysfunction, and limitations in their ability to work and participate in activities [14]. To measure health status outcomes, Clinical Practice Guideline for Chronic Kidney Disease recommends use of different methods and instruments to measure pain, QoL, health status, and functional status [14].

### Sample size

Sample size was estimated based on statistical considerations for a parallel trial and on previous studies that have paired noninvasive stimulation with chronic pain syndromes [9, 10, 15]. No previous studies have reported results about tDCS using a visual analog scale (VAS) or numeric rating scale (NRS) in CKD. G-Power 3.1.9.2 was used to calculate sample size. VAS is a 0–10-point scale and will be used as the primary outcome. Sample size calculation assumed a significance of 0.05 and power of 0.80. Fregni suggested in previous studies that a mean reduction of 3 points in VAS for the group under active stimulation was expected in contrast to no improvement in the sham group [15]. Sample size was estimated based on the assumption of significance of 0.05, power of 95%, with 0.40 effect size. According to this methodology the sample size would be 36 participants. We decided to add nine more patients to prevent any reduction of power in case of patient dropout. Thus, 45 patients will be recruited and randomized into three groups of 15 patients each.

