### Statistical analysis

Statistical analyses will use SPSS (v.19.0, Chicago, USA) and Graph Pad Prism 5. Clinical and sociodemographic characteristics (marital status, income, education, and ethnicity) will be described by means and standard deviations for continuous numeric parameters, and by frequency tables with 95% confidence intervals for categorical parameters. Chi-squared test will compare the distributions of categorical variables. Kruskal-Wallis test and ANOVA will compare differences in final values between groups.

The Shapiro-Wilk and Levene’s test will assess the normality of the distribution and homogeneity of variance of the data, respectively. Non-parametric tests will be used in case of non-normality distribution. Mauchly’s test of sphericity will be used to validate the correlation of the repeated measures and where the assumption of sphericity is violated, the Greenhouse-Geisser correction will be applied. The effects of stimulation on primary and secondary outcomes will be calculated using a mixed ANOVA model. The dependent variable will be the score of each outcome, and the independent fixed variables will be the time of treatment (baseline, tenth day, first follow-up, and second follow-up), the group of stimulation (active and sham), and the interaction term time vs group. Post-hoc comparisons will be carried out using Bonferroni correction for multiple comparisons.

Friedman test will be used for non-parametric data. Missing data will be treated by intention-to-treat analysis, taking into account the method of the last observation carried forward. Partial η^2^ will be calculated as measures of effect size in the ANOVA results (main effects and interaction effects). Partial η^2^ will be used to calculate the effect size, where η^2^ = 0.01 will be considered small, η^2^ = 0.06 moderate, and η^2^ = 0.14 large effect. Statistical significance will be set at *p* value less than 0.05.

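### The sample-size paragraph gives two powers, 0.80 and 95%, for one N of 36, and at effect size 0.40 neither carries over to a single-visit comparison of the three groups

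*Protocol article*

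**What the plan says.** The Sample size section names the software but not the test: "G-Power 3.1.9.2 was used to calculate sample size". It states the error rates once as "Sample size calculation assumed a significance of 0.05 and power of 0.80". It then gives the clinical premise, "a mean reduction of 3 points in VAS for the group under active stimulation was expected in contrast to no improvement in the sham group", with no standard deviation. The error rates follow a second time, with a different power: "Sample size was estimated based on the assumption of significance of 0.05, power of 95%, with 0.40 effect size". The result is "According to this methodology the sample size would be 36 participants", and nine patients are added for dropout, giving three groups of 15.

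The Statistical analysis section plans two kinds of group comparison. One sentence reads "Kruskal-Wallis test and ANOVA will compare differences in final values between groups". The next paragraph assigns the effect of stimulation on the primary and secondary outcomes to a mixed ANOVA over four time points with a time-by-group term, followed by Bonferroni-corrected post-hoc comparisons.

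**The concern.** A power of 0.80 and a power of 95% are different design targets and need different numbers of patients under the same test. The paragraph reports both and arrives at one N, so at least one of the two does not describe the calculation that was run.

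The second issue is what the retained figure would mean. The primary objective concerns M1 and DLPFC stimulation, so it is answered by comparing each active arm with sham. A reader who sees 95% power will apply it to those comparisons. If it belongs to an omnibus interaction test under particular options, a null result could be taken as stronger evidence of no effect than the design supports. The Discussion says the trial should guide a larger multicentre study, so the misreading could be carried forward.

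**Working it through.** **Inputs from the protocol.** Alpha 0.05; power 0.80 and 95%; effect size 0.40; N = 36 before and 45 after the dropout allowance; three equal groups; four measurement times; expected VAS difference 3 points against none in sham.

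**Assumptions.** The 0.40 is read as Cohen's f, the ANOVA metric in G-Power. The correlation rho between repeated scores, the SDs and sphericity are not given in the protocol; values used are marked. Required N is the smallest multiple of three that reaches the power.

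**1. Dropout step.** 9/45 = 20%, and 36/(1 − 0.20) = 45. This is consistent.

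**2. Reproducing 36.** For the group-by-time interaction with k = 3 groups and m = 4 times, noncentrality is lambda = f² × N × m/(1 − rho), with (k − 1)(m − 1) = 6 and (N − k)(m − 1) degrees of freedom.
- rho = 0, N = 36: lambda = 0.16 × 36 × 4 = 23.04 on 6 and 99 df; power 95.8%. N = 33 gives 93.6%, so 36 is exactly the 95% figure.
- rho = 0, 80% power: N = 24 (81.0%; N = 21 gives 73.8%).
- rho = 0.25, N = 36: power 99.2%. rho = 0.5, N = 36: above 99.9%, and 21 patients reach 95%.
- Effect-size convention of SPSS, lambda = f² × (N − k)(m − 1) = 0.16 × 33 × 3 = 15.84: power 83.9% at N = 36. Here 36 is the 80% figure and 51 is needed for 95%.

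Other option sets also reach 36, so a match shows a possible origin only. Within each set, the N for 80% and the N for 95% differ.

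**3. Three groups at one visit.** One-way ANOVA, lambda = f² × N on 2 and N − 3 df.

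| N | lambda | power |
|---|---|---|
| 36 | 0.16 × 36 = 5.76 | 52.5% |
| 45 | 0.16 × 45 = 7.20 | 63.5% |
| 66 | 10.56 | 81.8% |
| 102 | 16.32 | 95.5% |

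For this test, 66 patients are needed for 80% and 102 for 95%.

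**4. From 3 points to 0.40.** If both active arms improve by d SDs and sham by none, the one-way f is d × √(2/9). With f = 0.40, d = 0.40/0.471 = 0.849, so 3 points implies SD = 3/0.849 = 3.54. For the interaction, with that effect held at the three post-baseline times, f = d × √(2/9 × 3/16) = 0.204d. Then d = 1.96, and 3 points implies SD = 3/1.96 = 1.53. The same 0.40 thus stands for very different clinical effects depending on the test.

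**5. Active versus sham, 3-point difference.** Two-sample t test, two-sided, noncentrality (3/SD) × √(n/2) on 2n − 2 df. For example, n = 12 and SD 2.5 give 1.2 × √6 = 2.94 on 22 df. The SDs are assumed.

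| alpha per comparison | n per arm | SD 2 | SD 2.5 | SD 3 |
|---|---|---|---|---|
| 0.025 (two comparisons) | 12 | 88.9% | 70.1% | 52.7% |
| 0.025 | 15 | 95.3% | 81.5% | 64.6% |
| 0.0167 (three comparisons) | 12 | 85.0% | 63.8% | 45.9% |
| 0.0167 | 15 | 93.3% | 76.5% | 58.1% |

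**The case against.** The best defence is that the mixed ANOVA, not the one-way test, is the analysis assigned to the primary outcome. The sentence on final values closes a paragraph about describing patient characteristics and names no outcome. For the interaction in the mixed model, 36 patients reach the stated 95% at rho = 0 and exceed it at any positive rho under the same option. Zero correlation between a patient's repeated VAS scores is implausible, but in that option it is conservative. Even the less favourable convention gives 83.9%, above 0.80. All of this stands. A reader might infer from the 66 or 102 of the one-way test that 36 is an arithmetic error; the document does not support that.

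A reader might also infer that an SD of 3.54 is impossible because eligibility requires a VAS above 4, which would cap the SD near 3. That bound concerns baseline scores. Final scores can fall anywhere from 0 to 10, so it does not apply to them. The pattern with both active arms improving by 3 is itself an assumption.

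Nor does the document establish that the trial is underpowered for 3 points. A one-way test of that effect with 36 patients would have 96% power at SD 2 and 84% at SD 2.5. Finally, a condensed article may leave the test, SD and correlation to the full protocol, so their absence alone is no fault. None of this removes the printed conflict between two powers.

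**Conclusion.** Wrong as written. The paragraph states 0.80 and 95% for one N, and none of the single option sets examined requires 36 for both: 24 or 36 for the interaction at rho = 0, 36 or 51 under the SPSS convention, 66 or 102 for the one-way test. The 95% can be recovered for the interaction at rho = 0, so the conflict lies in the statement of power and not demonstrably in the 36.

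The statement that 36 delivers neither power is limited to a single-visit comparison of the three groups at f = 0.40, where power is 52.5%, or 63.5% if all 45 are evaluable. For the active-versus-sham comparisons, power depends on an SD that the protocol does not give and on how many comparisons the Bonferroni correction covers. With 12 per arm and a 3-point difference it lies between 46% and 89% over the assumed SDs of 2 to 3. These results rest on reading 0.40 as Cohen's f and on three separate groups in the model.

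**What to change.** Keep N = 45. Delete one of the two powers. State the retained one with its test, effect-size metric and assumed correlation; if it came from the group-by-time interaction, say that it is the power of that test only. Give the SD that links 3 points to the chosen effect size.

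Add one sentence with the power of the active-versus-sham VAS comparisons at the Bonferroni level that the plan will actually use, taking the matching rows of the last table: alpha 0.025 if only the two comparisons with sham are made, 0.0167 if all three pairs are. The plan does not yet say which, so that choice must be made first; inserting a 0.025 figure without it would introduce a new mismatch.

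The cost is the rewording of one paragraph. No patients are added and the design does not change. The downside for the sponsor is that the stated power becomes less favourable.

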### Randomization method

Eligible and consenting patients will be randomized using the order of entry into the study and a previous computer-generated randomization list, using random blocks of six patients (for each six patients, two will be randomized to each group) to minimize the risk of unbalanced group sizes. A research assistant external to the study will generate the allocation sequence. Each participant will be equally likely to belong to any one of the groups. Opaque envelopes will be used to conceal allocations. Participants and researchers involved in the assessments and interventions will be blind to group allocation throughout the trial.

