### Blinding

Patients and evaluating researchers will be blinded. To ensure patient blinding, the electrodes of the sham group will be placed in the same position as for active groups. The anodal electrode will be placed over the motor cortex and the cathodal over the contralateral supraorbital area, according to placement procedures described below. Usually when the current initiates, patients report itching or a tingling sensation under the electrodes for 2 or 3 minutes. This method of sham intervention is therefore designed to provide an initial period of tingling so that similar sensations are perceived as during active tDCS [11]. For the placebo group a ramp-up of 30 s and a ramp-down of 30 s will be used. The device displays are identical in active and sham settings. To ensure the success of blinding, we will ask participants and outcome assessors at the endpoint to guess whether the treatment was active or sham. Researchers involved in the assessments will be blinded to group allocation throughout the trial.

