**Fig. 2 Fig2:**
[figure not shown]
Illustration of electrode replacement. **a** M1 group. The anodal electrode will be placed over the motor cortex and the cathode over the supra-orbital contralateral area (C3/Fp2 montage). **b** DLPFC group. The anodal electrode will be placed over the DLPFC and the cathode over the supra-orbital contralateral area (F3/Fp2 montage). Electrodes will the placed according to 10/20 EEG international system. Electrode size 35 cm^2^ with a current density of 0.057 mA/cm^2^

During the baseline period, patients will be randomized at a ratio of 1:1:1 to receive sham tDCS (sham group), active tDCS of the primary motor cortex (M1 group), or active tDCS of the left DLPFC (DLPFC group). The M1 was chosen because studies show that stimulation of this area is associated with pain improvement [9, 11, 15, 16]. The left DLPFC was chosen because several studies with neuromodulation have shown that stimulating this area is associated with improvement of depression and also induces an analgesic effect in fibromyalgia [9, 15]. The electrodes will be placed into a 35 cm^2^ square sponge immersed in saline solution (150 mMols of NaCl diluted in water Milli-Q). For stimulation, a gradual current ramp-up and ramp-down with 30-s duration will be used. Electrodes attached to the scalp will be supported by an elastic band. The electrodes (anode and cathode) will be connected to a battery-powered (9 v) stimulator with current verified by a precision digital multimeter (DT832, WeiHua Electronic Co., Ltd, China) with standard error of ±1.5%.

For ethical reasons, no changes will be made to HD routines (days and the place of sessions), clinical care (medicines, imaging, or blood exams), and previous prescription of painkillers or other medication.

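### One fixed, disclosed block size of six makes some allocations foreseeable to anyone who sees the electrode montage, and it does not divide 45, so 15/15/15 is not assured: a minor weakness that is cheap to fix.

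*Protocol article*

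**What the plan says.** All places are in the Protocol article.

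- **Randomization method:** the computer-generated list is read in order of entry, "using random blocks of six patients (for each six patients, two will be randomized to each group", and the stated purpose is "to minimize the risk of unbalanced group sizes". Someone outside the study generates the sequence, opaque envelopes conceal it, and participants and the researchers doing assessments and interventions are said to be blind.
- **Sample size:** "Thus, 45 patients will be recruited and randomized into three groups of 15 patients each".
- **Intervention:** "patients will be randomized at a ratio of 1:1:1".
- **Study design and recruitment:** "This study is a single-center, parallel, randomized, sham-controlled trial in which patients and assessors will be blinded". No strata are mentioned, so there is one list.
- **Blinding:** sham electrodes are said to go where the active ones go, and the position then given is a single one: "The anodal electrode will be placed over the motor cortex and the cathodal over the contralateral supraorbital area". Device displays are the same for active and sham.
- **Fig. 2 legend, DLPFC group:** "The anodal electrode will be placed over the DLPFC and the cathode over the supra-orbital contralateral area (F3/Fp2 montage". The M1 group has its anode at C3.

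**The concern.** With one constant, known block size, the last places in each block follow from the earlier ones. Opaque envelopes hide the next slip, but they do not prevent deduction from earlier allocations that can be seen. In this trial part of each allocation is visible: an F3 anode means DLPFC, and a C3 anode means M1 or sham. If that knowledge reached whoever decides which patient enters next, or when, entry could depend on the expected arm. Blinded assessment afterwards cannot undo selection at entry.

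The block size and the sample size also do not fit together. A list of 45 in blocks of six stops in the middle of the eighth block, so the stated arm sizes are a target that the method does not guarantee.

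**Working it through.** **Inputs.** Block of six with two per arm (Randomization method); N = 36 + 9 = 45 and 45/3 = 15 per arm (Sample size), which reproduces the plan's figures; sham in the M1 position (Blinding); DLPFC at F3 (Fig. 2 legend).

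**Enumeration.** A 2:2:2 block has 6!/(2!·2!·2!) = 90 equally likely orders. For each place in the block, count the orders in which the observer's information on the earlier places leaves one possibility. Over 45 patients the total is 7 full blocks plus the first three places of an eighth.

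| Observer knows → can call | Forced orders out of 90, places 1 to 6 | Expected per block | Share of a full block | Over 45 patients |
|---|---|---|---|---|
| Montage of earlier patients → DLPFC or not | 0, 0, 6, 18, 42, 90 | 156/90 = 1.733 | 28.9% | (7 × 1.733 + 0.067)/45 = 12.2/45 = 27.1% |
| Montage of earlier patients → exact arm | 0, 0, 0, 0, 6, 30 | 36/90 = 0.4 | 6.7% | (7 × 0.4)/45 = 2.8/45 = 6.2% |
| Exact arm of every earlier patient in the block → exact arm | 0, 0, 0, 0, 18, 90 | 108/90 = 1.2 | 20.0% | (7 × 1.2)/45 = 8.4/45 = 18.7% |

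Of the 28.9% montage calls, 6.7 points are certain DLPFC. The other 22.2 points are certain not-DLPFC, which leaves M1 against sham open.

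**Comparator for the montage row.** Always guessing not-DLPFC is right 67% of the time. Best use of the montage history gives (3 × 0.667 + 2 × 0.733 + 1)/6 = 74% over a full block.

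**Balance.** 45 = 7 × 6 + 3. The first 42 patients are exactly 14/14/14. The last three are a random three of a 2:2:2 block, so P(one of each) = (2 × 2 × 2)/C(6,3) = 8/20 = 0.40. Otherwise (0.60) the split is 16/15/14 in some order, which is also the worst case.

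**Cost of 16/15/14.** The variance of a two-arm difference is proportional to 1/n₁ + 1/n₂. For 15 and 15 this is 0.1333; for the worst pair, 15 and 14, it is 0.0667 + 0.0714 = 0.1381. The standard error rises by √(0.1381/0.1333) = 1.018, under 2%.

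**Effect of mixed blocks.** With three blocks of six and three of nine in random order (3 × 6 + 3 × 9 = 45), arm totals are 3 × 2 + 3 × 3 = 15 each, always. Simulating an observer who still assumes blocks of six, the calls that seem certain are right about 63% of the time with full knowledge of earlier arms and about 75% with montage only. Under the present list both are 100%.

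**The case against.** Permuted blocks with external generation and opaque envelopes are a conventional design. The article aims only to limit imbalance and does not promise exact equality, and dropout will unequalise the completers anyway. A trained physician delivers the sessions, while the study explanation and consent are given by a research coordinator and the research team; nothing says that the person who places electrodes decides who enters next. All of this stands. It limits the point to a conditional and minor one.

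A reader might infer that about one allocation in five is known in advance. The documents do not support that. It requires the exact arm of every earlier patient in the block, and the montage never separates M1 from sham; the envelopes and identical device displays make that knowledge unlikely.

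A reader might also infer that publishing the block size exposed the sequence. The article gives a registration date and a publication date but does not say whether recruitment was still open, so this cannot be judged.

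What the objection does not remove is that the montage is visible without any unblinding, and that the article itself fixes both the block size and a sample size that it does not divide.

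**Conclusion.** The point holds as a minor weakness. Staff who see the electrodes could call about 27% of the 45 allocations DLPFC or not-DLPFC with certainty, and the exact arm for about 6%. This assumes that sham is always in the M1 position, as the Blinding section describes it, that someone tracks the order of entry and the block boundaries, and that this person has some influence on enrolment. The last is not stated either way. Selection bias is therefore possible but not shown.

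The mismatch between blocks of six and 45 patients is certain but nearly harmless: 15/15/15 has probability 0.40, and the worst outcome, 16/15/14, has a negligible effect on power.

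The visible DLPFC montage also sits badly with the statement that intervention researchers are blind. That is a separate question about blinding and adds nothing to the size of this one.

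**What to change.** Have the external list-maker use randomly ordered blocks of six and nine that total 45, for example three of each. Keep block sizes out of documents available to site staff until enrolment closes. The stated 15/15/15 is then exact if all 45 are randomised.

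If recruitment has begun, complete the block of six in progress and fill the remainder up to 45 with a random mix of block sizes that are multiples of three. The remainder is always a multiple of three, because both 45 and 6 are.

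The cost is a new list and one sentence of protocol text, with no extra patients or staff. The downside is a slightly larger temporary imbalance inside a block of nine. Predictability falls but does not vanish, as the 63% and 75% above show.
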